### 3.3. Epigenetic Variables

For the epigenetic analysis, circulating microRNAs will be isolated from venous blood samples using the mirVana™ miRNA Isolation Kit (Thermo Fisher Scientific, Waltham, MA, USA). Fourteen microRNAs related to inflammation, adipogenesis, and fatty acid metabolism will be analyzed. Specific amplification of each microRNA will be performed using the QuantStudio 3 system (Thermo Fisher Scientific, Waltham, MA, USA), and expression levels will be quantified using the ∆∆Ct method with TaqMan MicroRNA Assays (Thermo Fisher Scientific, Waltham, MA, USA). Additionally, genotyping of polymorphisms related to obesity and lipid metabolism will be performed using TaqMan probes with a StepOnePlus thermocycler (Thermo Fisher Scientific, Waltham, MA, USA).

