#### 4.5.3. Epigenetic Variables

To measure circulating microRNAs, peripheral venous blood samples will be collected in EDTA vacutainer tubes (5 mL). Subsequently, the mirVana™ miRNA Isolation Kit (Thermo Fisher Scientific, Waltham, MA, USA) will be used to analyze 14 microRNAs involved in inflammatory processes (miR-15, miR-29c, miR-30^a^, miR-142/3, miR-181^a^), adipogenesis (miR-188-5p, miR-146b-5p, miR-103, miR-107, miR-125b), and fatty acid metabolism (miR-33, miR-335, miR-370, miR-758).

Additionally, cDNA synthesis will be carried out through the reverse transcription of the microRNAs using the TaqMan MicroRNA-RT Kit (Thermo Fisher Scientific, Waltham, MA, USA). Specifically, amplification of the microRNAs of interest will be performed using the TaqMan Universal Master Mix II with UNG reagent (Thermo Fisher Scientific, Waltham, MA, USA). The specific amplification of each microRNA will be conducted with the QuantStudio 3 system (Thermo Fisher Scientific, Waltham, MA, USA), using probes specific to each microRNA and their internal controls through the TaqMan MicroRNA Assays MTO LG chemistry (Thermo Fisher Scientific, Waltham, MA, USA). The relative quantification of expression levels will be performed using the ∆∆Ct quantification method, validated through the quantification of amplification efficiency and the construction of a dynamic range curve.

In turn, the genetic influence on anthropometric and biochemical changes after the treatments will be evaluated using TaqMan probes (Thermo Fisher Scientific, Waltham, MA, USA) through an RT-PCR system using a StepOnePlus thermocycler (Thermo Fisher Scientific, Waltham, MA, USA). The polymorphisms to be assessed will include those related to obesity (rs9939609, *FTO*), lipid metabolism (rs1799883, *FABP2*), and physical adaptation to exercise (R577X, *ACTN3*). Genotyping will be verified using positive controls corresponding to the three possible genotypes in each experiment.

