#### 4.5.5. Data Analysis

The normality and homoscedasticity of the variables will be assessed using the Kolmogorov–Smirnov and Levene tests for each group. A student’s *t*-test will be used to analyze the differences between the pre- and post-treatment values for each variable if the data follows a normal distribution. If the data are non-parametric, the Mann–Whitney U test will be used. Statistical analysis between treatments will be conducted using ANOVA with Tukey’s post-hoc test in the case of parametric distribution and/or Kruskal–Wallis H and Dunn’s Post-hoc test for non-parametric distribution, with a Bonferroni setting for comparing intervention-induced changes. Additionally, Pearson and/or Spearman correlation tests will be used to establish associations between variables. Multivariate linear regression models will also be constructed to explore the contribution of treatment on main outcomes, which will be adjusted by potential confounder factors including age, sex, dietary variables, psychological variables, and baseline measurements. Moreover, multiple imputations will be used for generating replacement values for missing data. Statistical significance will be considered at *p* < 0.05, and all statistical analyses will be conducted using IBM SPSS package version 22 (SPSS Inc., IBM Company, Chicago, IL, USA) and GraphPad Prism v8.1 (GraphPad Software, La Jolla, CA, USA).

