## 5. Expected Results

International organizations widely promote physical activity and exercise to combat non-communicable chronic diseases, which are highly associated with obesity [1]. Unfortunately, most people do not meet the minimum requirements for participation in physical activity, particularly those who are overweight or obese and who express multiple limitations in adhering to recommendations. A constant barrier is the lack of knowledge on performing specific exercises [25]. In this regard, the Physical Activity Working Group of the European Association for this study of Obesity emphasized in 2021 the need for truly functional practical exercise recommendations that focus on managing overweight and obesity. It has been agreed that a moderate-intensity aerobic exercise training program promotes substantial improvements in both weight loss and the improvement of circulating lipids, total fat accumulation, and intra-visceral fat [26].

In this context, this study will elucidate how FatMax training, both alone and in combination with resistance exercises, can enhance metabolic flexibility, increase fat oxidation, and improve body composition. This study seeks to provide critical insights into the optimization of fat utilization and the reduction of visceral fat while simultaneously preserving lean muscle mass. Additionally, expected improvements in biochemical markers—such as enhanced insulin sensitivity, improved lipid profiles, and reduced systemic inflammation—will support the formulation of targeted exercise strategies to lower the risk of chronic diseases, including cardiovascular disease and type 2 diabetes. Furthermore, anticipated epigenetic changes, particularly in microRNAs associated with adipogenesis and inflammation, will offer novel perspectives on the molecular mechanisms activated by FatMax exercise. Together, these results will lay the groundwork for evidence-based, personalized exercise recommendations that address the specific metabolic and physiological needs of this population, ultimately contributing to more effective and sustainable approaches to obesity management.

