If these issues are not properly addressed, the consequences will have serious public health concerns. The prevalence of obesity will continue to rise, increasing the number of people at risk of developing chronic diseases, reducing their life expectancy, and quality of life. In addition, the health care system will face increased costs and pressure, making this silent pandemic even more difficult to manage.

As limitations of this study protocol, we cannot include a double or triple blind randomized trial, due the interventions are related to a FatMax and/or resistance training program and only the data analysis researcher will be blinded. Additionally, it is acknowledged that in addition to exercise, other lifestyle factors might influence microRNA expression, such as diet, sleep quality, emotional stress, or psychological variables, so we will include them in the correlation tests and multivariate linear regression model analysis.

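### Correlations are to establish associations at an uncorrected p < 0.05; a microRNA screen of the breadth the text suggests would be likely to label some chance links as established

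*Protocol article*

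**What the plan says.** All of the following is in the protocol article.

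- **Purpose of the correlations (4.5.5 Data Analysis).** "Pearson and/or Spearman correlation tests will be used to establish associations between variables". No pairs are listed and no number of tests is given.
- **Threshold (4.5.5).** "Statistical significance will be considered at *p* < 0.05". No separate level is set for the correlations.
- **Corrections (4.5.5).** Tukey and Dunn post-hoc tests, "with a Bonferroni setting for comparing intervention-induced changes". All of these belong to the sentence on analysis between treatments.
- **Regression (4.5.5).** "Multivariate linear regression models will also be constructed to explore the contribution of treatment on main outcomes". The exploratory verb is used here and not for the correlations.
- **MicroRNAs (3.3 Epigenetic Variables).** "Fourteen microRNAs related to inflammation, adipogenesis, and fatty acid metabolism will be analyzed". Section 4.5.3 names the 14.
- **Lifestyle variables (5 Expected Results, limitations paragraph).** Diet, sleep quality, emotional stress and psychological variables are named as possible influences on microRNA expression, "so we will include them in the correlation tests and multivariate linear regression model analysis".

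**The concern.** Section 4.5.5 fixes three things for the correlations: the aim (to establish), the threshold (0.05 per test) and, by where the corrections are placed, no adjustment. An analyst who follows it would report every correlation with p < 0.05 as an established association, however many were run.

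With 14 microRNAs on one side, the number of tests rises by 14 for each variable placed on the other side. No adjustment of the comparisons between arms reaches this error. What is at stake is the credibility of the links reported between microRNAs and lifestyle or metabolic variables, not the treatment effect on the primary outcome.

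**Working it through.** **No figure to reproduce.** The article gives neither a number of correlation tests nor an error rate for them. The only computed design figure is the sample size, which does not bear on this point.

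**Inputs**
- Per-test level: 0.05 (section 4.5.5).
- MicroRNAs: 14 (sections 3.3 and 4.5.3).
- Lifestyle domains entered in the correlation tests: 4, namely diet, sleep, stress and psychological variables (section 5).
- Named lifestyle measures: 7, namely calories, protein, carbohydrate and fat intake, two sleep questionnaires, and the DASS-21 counted once (section 4.5.4).
- Biochemical markers: 8, namely total cholesterol, HDL, LDL, triglycerides, glycosylated hemoglobin, glucose, IL-6 and TNF-α (sections 3.1 and 4.5.1).
- Number of tests m: **assumed**, built from these lists, one coefficient per pair.

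**Formulas**, if no association is real:
- Expected false positives = m × 0.05. This holds whatever the dependence between tests.
- Chance of at least one = 1 − 0.95^m. This assumes independent tests.

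| Assumed set | m | Expected false positives | Chance of at least one (independent) |
|---|---|---|---|
| 14 microRNAs × 1 variable | 14 | 14 × 0.05 = 0.7 | 51% |
| 14 × 4 lifestyle domains, one variable each | 56 | 56 × 0.05 = 2.8 | 94% |
| 14 × 7 named lifestyle measures | 98 | 98 × 0.05 = 4.9 | 99% |
| 14 × 8 biochemical markers | 112 | 112 × 0.05 = 5.6 | 99.7% |

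**Sensitivity to dependence.** The variables within each block are likely to be correlated. A simulation of the 14 × 8 case (1,000 datasets, 132 participants = 3 × 44, the two blocks unrelated to each other) kept the mean at 5.6 to 5.9 false positives. As the correlation within blocks rose from 0 to 0.5, the chance of at least one fell from 99% to 92%, and the chance of three or more fell from 93% to 66%. Dependence spreads the count more widely but does not remove the problem.

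**If some associations are real,** the expected number of false ones is 0.05 times the number of pairs with no true association, so it falls in proportion.

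**The case against.** **The pairs are not listed.** The 14 × 8 matrix appears nowhere in the article, and a narrow set of pairs would give few false positives (0.7 for 14 tests). This stands: the count is an assumption and has to be shown as a range. However, section 5 does put four lifestyle domains into the correlation tests because of their possible influence on microRNA expression. One variable per domain already makes 56 tests.

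**This is detail for the analysis plan.** Correlation families and false-discovery control for secondary analyses are commonly left to a statistical analysis plan, which is not shown here. Their absence alone would be no finding. But the article states an aim and a threshold and confines its corrections to the treatment comparisons. A later plan with false-discovery control would have to change that rule.

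**The analyses are secondary.** The correlations follow the treatment comparisons, and section 4.1 names body composition as the primary outcome. This stands and limits the weight of the point.

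**Stronger readings that the text does not support**
- A reader might infer that genotype tests, too, are meant to establish associations. Section 4.5.3 says only that "the genetic influence on anthropometric and biochemical changes after the treatments will be evaluated using TaqMan probes". Section 4.5.5 names no genotype test, and its correlation sentence does not mention genotype.
- A reader might infer that every variable will be correlated with every other. The text does not say so.
- A reader might infer that chance correlations would be reported as mechanism. Section 5 says that anticipated changes in microRNAs "will offer novel perspectives on the molecular mechanisms activated by FatMax exercise"; it does not tie mechanism to the correlations.
- A reader might take *and/or* to mean that each pair is tested with both coefficients. The preceding sentence of section 4.5.5 on treatment comparisons uses the same words for a choice by distribution, which is the natural reading here as well. There is no ground to require one coefficient throughout.

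**Conclusion.** The point holds as one about the stated purpose and threshold of a secondary analysis. Followed as written, section 4.5.5 would count any correlation with p < 0.05 as established, and none of its corrections covers these tests. For a microRNA screen of the breadth that section 5 suggests, about 2.8 false positives are expected with 56 tests and 5.6 with 112; with only 14 tests it is 0.7. These figures assume that no association is real, and the test counts are built from the article's variable lists because it names no pairs. Some chance findings are therefore likely, but their number cannot be fixed from the document. The primary body-composition comparison and the between-arm conclusions are untouched.

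**What to change.** In section 4.5.5:

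1. Write *explore* in place of *establish* for the correlations, matching the verb already used for the regression models.
2. State that the correlation results are hypothesis-generating.
3. Name the microRNA correlation families (for example microRNA by lifestyle variables and microRNA by biochemical markers) and apply Benjamini-Hochberg false-discovery control at 5% within each. Do the same for genotype associations if they are tested.

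**Cost.** Wording and a simple adjustment of p-values, with no change to data collection, sample size or conduct. The small downside is that fewer associations will be called significant. As an outer bound, full Bonferroni over 112 tests (0.05/112 = 0.00045) with 132 participants would raise the smallest significant correlation from 0.171 to 0.301. Benjamini-Hochberg is never stricter than that.

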It should be noticed that 8 to 20 weeks of FatMax training seem to not alter free fat mass or muscle mass in this population [7,9]. Therefore, combining FatMax training with resistance exercises may increase the lean mass of subjects with obesity, preventing sarcopenic obesity and cardiometabolic disorders related to low muscle mass over the long term [9,10]. On the other hand, it has been demonstrated that fat oxidation during exercise is determined by age, sex, body fat levels, genotype, and the type of exercise in individuals with obesity [11,12]. However, the influence of these moderators on the cardio-metabolic adaptations stimulated by FatMax training remains understudied. In addition, there is scarce information about the molecular mechanisms that become activated by FatMax training to induce positive adaptations in metabolic function and overall fitness. To be precise, Bogdanis et al. [13] and Tan et al. [14] reported that skeletal muscle mitochondrial respiratory capacity and the activity of lipoprotein lipase increased significantly after 10 weeks of FatMax training in overweight and obese individuals. Nevertheless, the impact of FatMax training on epigenetic biomarkers related to mitochondrial biogenesis and the regulation of fatty acid metabolism, such as microRNAs, remains unexplored. In this context, microRNAs such as miR-1, which regulates the expression of CPT1, a key enzyme in the transport of fatty acids to the mitochondria, and miR-145, miR-20a-5p, and miR-29a, which modulate the activity of CD36, a protein involved in the uptake of long-chain fatty acids, have been linked to the development of obesity due to their role in lipid metabolism regulation. However, exploring how these microRNAs can be modified by physical exercise interventions, such as those performed at the intensity of maximal fat oxidation (FatMax), is essential to better understand the underlying molecular mechanisms that could optimize both the prevention and treatment of obesity, thereby enhancing intervention strategies to promote overall well-being [11].

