### 2.3. Interventions or Treatments

Participants will be randomly assigned to one of three groups: Group A: Will perform low-intensity training within the FatMax zone. Group B: Will perform FatMax training combined with resistance exercises. Group C (Placebo Group): The placebo group will undergo a ‘masking training’ that does not involve significant physiological or metabolic changes. This training will consist of stretching sessions with smooth, controlled movements that do not significantly impact metabolism or induce relevant physiological changes, while maintaining the perception of physical activity and an isoenergetic diet.

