## 4. Detailed Procedure

### 4.1. Sample Size Calculation

To carry out the present study, 156 young sedentary adults with overweight/obesity will be recruited through a snowball sampling. Considering the body composition changes as the primary outcome, the minimum sample size calculated for the present protocol was 44 participants to reliably detect an effect size of δ ≥ 0.5, assuming a two-sided criterion for detection that allows a maximum Type I error rate of α = 0.05 with a probability of 0.9, and considering a 20% dropout of participants, the sample size has been fixed to 52 participants per group. The statistical software used to determine the sample size was G*Power (v3.1.9.7, Universität Kiel, Düsseldorf, Germany) [15]. 

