### 4.2. Randomization and Blinding

The protocol involves the assignment of 52 subjects to one of three groups. Group A will comprise participants performing low-intensity training sessions within their FatMax zone. Group B will comprise participants who will perform both FatMax zone exercises as well as muscular resistance exercises (MRE). Both groups will be compared to group C, where participants will maintain their physical activity following an isoenergetic diet, evaluated through 24 h dietary records every four weeks.

For groups A and B, subjects will be allowed to perform their FatMax training on a treadmill or stationary bicycle, whichever is of their preference. The random sequence for participant assignment will be coded with SPSS 22 Software, looking for an equal distribution of both genders, BMI (overweight (≥25 and <30 kg/m^2^) and obesity grade 1 (≥30 and <35 kg/m^2^). All the evaluations and training sessions will be conducted in the Conahcyt National Laboratory of Body Composition and Energetic Metabolism (LaNCoCoME). The general process is shown in Figure 1.

To ensure single blinding, a researcher external to this study will enter data into the software on separate datasheets so that these researchers can analyze them without having access to treatment assignment information, storing all participant files in numerical order in a secure and accessible location. All files will be retained for a period of five years.

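### Associations are to be established by unadjusted Pearson/Spearman correlations in a two-sex, three-arm sample; no stated analysis removes sex or arm as a shared cause

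*Protocol article*

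**What the plan says.** Section 4.5.5 (Data Analysis) gives one sentence to associations: "Pearson and/or Spearman correlation tests will be used to establish associations between variables". The section's general threshold of p < 0.05 applies. No partial, stratified or within-arm version is named. The text does not say which variables are paired, whether baseline, post or change values are used, or whether sexes and arms are pooled.

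The next sentence brings in adjustment for a different purpose: "Multivariate linear regression models will also be constructed to explore the contribution of treatment on main outcomes". Those models are to be "adjusted by potential confounder factors including age, sex, dietary variables, psychological variables, and baseline measurements".

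The limitations paragraph in section 5 (Expected Results) recognises that diet, sleep quality, emotional stress and psychological variables may influence microRNA expression, and continues: "so we will include them in the correlation tests and multivariate linear regression model analysis". Sex and arm are not in that list.

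On the sample, section 2.3 says "Participants will be randomly assigned to one of three groups", and two of the three groups train. Section 4.2 describes the allocation as "looking for an equal distribution of both genders". The Introduction states that "fat oxidation during exercise is determined by age, sex, body fat levels, genotype, and the type of exercise in individuals with obesity", and hypothesises that training will change body composition, fat oxidation and epigenetic markers together.

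**The concern.** A Pearson or Spearman coefficient computed across subgroups mixes two things: the link between the variables inside each subgroup, and the differences between subgroup means. If both variables have different means in men and women, or both shift in the trained arms and not in the control arm, the second part alone produces a correlation. Correcting for multiple testing does not remove it, and a larger sample makes it more likely to reach significance.

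The article itself points to both shared causes. It names sex as a determinant of fat oxidation, and its hypothesis is that training moves several outcome families at once. At stake is a report that a microRNA and a fat measure are associated when, among people of the same sex in the same arm, they are not.

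**Working it through.** **Inputs from the article.** There are three arms, two of which train (section 2.3). Section 4.1 gives a total of 156, 52 per group, a minimum of 44 and an effect size of 0.5. Section 4.5.5 gives the threshold p < 0.05.

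**Assumptions.** The article gives no sex gap for any variable and no sex ratio. Sex gaps are varied from 0.5 to 2 SD, training responses from 0.3 to 1.5 SD, and the sex split from 50:50 to 80:20. Correlations are taken as pooled. The two variables are independent within every sex and arm, and both carry the same gap.

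**Sample size used.** The article states no figure for the correlations. Its minimum of 44 reproduces as a paired t-test (d = 0.5, two-sided 5%, power 0.900). It is used here only to set n = 3 × 44 = 132 completers. The sample-size calculation is not at issue.

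**Formulas.** If a fraction p of participants is shifted by d SD in both variables, and q = 1 − p, the induced correlation is

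r = pq·d² / (1 + pq·d²).

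The chance of p < 0.05 follows from Fisher's z: atanh(r)·√(n − 3) compared with ±1.96, with √129 = 11.36.

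**Shared sex difference, 50:50 (pq = 0.25), n = 132**

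| Gap in both variables | Induced r | Chance of p < 0.05 |
|---|---|---|
| 0.5 SD | 0.06 | 10% |
| 0.8 SD | 0.14 | 35% |
| 1.0 SD | 0.20 | 63% |
| 1.5 SD | 0.36 | 99% |
| 2.0 SD | 0.50 | about 100% |

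For the 1 SD row: r = 0.25/1.25 = 0.20; atanh(0.20) = 0.2027; 0.2027 × 11.36 = 2.30; P(Z > 1.96 − 2.30) ≈ 0.63. With all 156 participants the figure is 71%.

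**Uneven sex split, 1 SD gap.** At 70:30, r = 0.21/1.21 = 0.17 and the chance is about 51%. At 80:20, r = 0.16/1.16 = 0.14 and the chance is about 35%.

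**Shared training response, two arms of three (pq = 2/9), n = 132**

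| Response in both variables | Induced r | Chance of p < 0.05 |
|---|---|---|
| 0.3 SD | 0.02 | 6% |
| 0.5 SD (the design effect) | 0.05 | 9% |
| 0.8 SD | 0.125 | 30% |
| 1.0 SD | 0.18 | 55% |
| 1.5 SD | 0.33 | 98% |

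**Simulation check (20,000 trials, n = 132).** The unadjusted rates were 66% for a 1 SD sex gap and 9% for a 0.5 SD training response, close to the formula. A 1 SD sex gap combined with a 0.5 SD response gave mean r = 0.23, significant in 79%. The partial correlation given sex and arm had a mean near 0.00 and was significant in 4.9% to 5.2% in every scenario run.

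**Which values are exposed.** Baseline values can carry a sex gap but not a training response. Post values can carry both. Change values carry the training response; a stable sex difference in level cancels. The sex table therefore describes correlations of levels, not of change with change.

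**The case against.** **Pooling is not stated.** The sentence is silent on strata and time point. Correlations run within arm and sex would be free of the problem, and baseline correlations cannot be induced by training. A condensed article may leave such detail to the analysis plan. This stands as a limit on the claim. It does not dispose of it, because the article does fix the type of test, its purpose and its threshold, and the test it names adjusts for nothing.

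**The authors do address confounding.** They plan a regression that adjusts for sex, and section 5 promises to bring lifestyle and psychological variables into the correlation tests. The regression, however, is stated to serve treatment effects. Adding variables to a set of pairwise correlations does not adjust for them, and even if partial correlations are meant, sex and arm are not listed.

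**The large figures need large gaps.** This stands. The article names sex as a determinant of fat oxidation but does not say that microRNAs differ by sex, and if only one variable differs the induced correlation is zero. A reader might also infer that the design fixes an even sex split. Section 4.2 concerns allocation to groups, recruitment is by snowball sampling, and no sex quota is given; 50:50 is the split that maximises the effect.

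**The mechanistic conclusions may not depend on the correlations.** A reader might infer from section 5 that they do. The text there speaks of anticipated epigenetic changes, and section 4.5.5 compares intervention-induced changes between arms by ANOVA or Kruskal–Wallis. No sentence assigns the mechanistic conclusion to the correlations.

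**Adjusting for arm discards signal.** If the question is whether two measures move together because of training, arm adjustment removes that part. This is a fair point about the target of the analysis and is taken up under the fix.

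**Conclusion.** The concern holds as a matter of method. The plan names only unadjusted correlations for establishing associations, and none of its stated analyses removes sex or arm as a common cause of a variable-to-variable link.

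Such links can arise; the documents do not support saying that they will. Under pooling, sex is potentially the larger source, for baseline or post values: about 63% false positives at an assumed 1 SD gap in both variables and an even split, 51% at 70:30, and only 10% at a 0.5 SD gap. A shared training response at the protocol's own 0.5 SD is a small problem, about 9% against a nominal 5%. It becomes serious only towards 0.8 to 1 SD (30% to 55%).

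All of these figures rest on assumed gaps and on pooling. The correlations are secondary, and the randomised comparison between arms is untouched. This is an inexpensive improvement worth making, not a threat to the trial's main result.

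**What to change.** In section 4.5.5, replace the raw correlation tests by partial correlations (rank-based where needed) or regression slopes. Adjust for sex and BMI category in every case, and also for arm when post or change values are used. State which values each association uses. Raw pooled correlations may still be shown, labelled descriptive or exploratory, and the claim that they establish associations should go.

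Add one sentence on interpretation: the arm-adjusted estimate describes association within arm only, and any shared response to training is to be read from the between-arm comparisons.

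The cost is wording and a small change to the analysis. Sex, BMI category and arm are already recorded. The adjustment uses 1 + 1 + 2 = 4 degrees of freedom, leaving 126 of 130 at n = 132.
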